#### Analysis of loss of viral suppression

Besides severe events, we are interested in assessing the value of TS and CQ prophylaxis in preventing loss of viral suppression. As for the first occurrence of a severe event, separate comparisons of (1) TS continuation and discontinuation, (2) TS continuation and CQ prophylaxis, and (3) CQ prophylaxis and TS discontinuation will be done using Cox regression modeling to estimate two-sided 95 % CIs for treatment effects, expressed as HRs. Since severe events are expected to occur mainly in participants who do not maintain their viral suppression (i.e., who develop a detectable viral load), we define minimally acceptable prophylaxis, as for the occurrence of a severe event, as at least a 35 % effect in preventing loss of viral suppression. Then the same numbers of losses of viral suppression are needed for 80 % power to obtain a CI for effect of prophylaxis with upper bound less than 35 %, assuming there is no effect, as for the first occurrence of a severe event. We expect the probability of maintaining viral suppression to be approximately 75 % for participants taking TS prophylaxis who have the average amount of follow-up (49 months) [21]. Then about 75 participants in each of the study arms will be expected to lose their viral suppression during the study. The power to obtain an upper confidence limit less than 35 % for effect of prophylaxis is then about 75 % for each of the comparisons.

Intention-to-treat analysis will be used for all primary comparisons. This analysis will include all participants who were randomized, regardless of attendance at follow-up visits and the duration of study drug administration. For participants who are no longer being actively followed at the end of the study, every effort will be made to obtain their vital status. Per-protocol analysis will be performed as a secondary analysis for those who complied with follow-up visits at least every 8 weeks and for study and ART medication. Analyses will be done in which data on study volunteers who switch from one study intervention to another are censored at the time that they develop an indication for TS prophylaxis, regardless of treatment assignment.

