### Overview of the trial

A randomized, controlled, open-label, phase III trial of continued standard of care prophylaxis with daily TS compared to (1) discontinuation of standard of care TS prophylaxis and starting weekly chloroquine (CQ) prophylaxis, or (2) discontinuation of standard of care TS prophylaxis.

Study aim: to assess the need for antimicrobial prophylaxis in HIV-infected adults taking ART in sub-Saharan Africa.

Intervention: continue daily TS, stop daily TS, or stop daily TS and start weekly CQ.

Randomization: 1:1:1 to each study intervention, using block randomization and stratified by site.

Primary endpoint: the occurrence of a severe event (WHO stage 3 or 4 event or death, see Table 1).

**Table 1 Tab1:** Revised World Health Organization clinical staging for HIV/AIDS for adults and adolescents with confirmed HIV infection

Clinical stage 2
• Moderate unexplained weight loss (5–10 % of presumed or measured body weight)
• Recurrent respiratory tract infections (sinusitis, tonsillitis, otitis media and pharyngitis)
• Herpes zoster
• Angular cheilitis
• Recurrent oral ulceration
• Papular pruritic eruptions
• Seborrhoeic dermatitis
• Fungal nail infections
Clinical stage 3
• Unexplained severe weight loss (>10 % of presumed or measured body weight)
• Unexplained chronic diarrhoea for longer than 1 month
• Unexplained persistent fever (above 37.5 °C intermittent or constant, for longer than 1 month)
• Persistent oral candidiasis
• Oral hairy leukoplakia
• Pulmonary tuberculosis
• Severe bacterial infections (e.g., pneumonia, empyema, pyomyositis, bone or joint infection, bacteremia, severe pelvic inflammatory disease)
• Acute necrotizing ulcerative stomatitis, gingivitis or periodontitis
• Unexplained anemia (<8 g/dl), neutropenia (<500/mm^3^) and/or chronic thrombocytopenia (<50,000/mm^3^)
Clinical stage 4
• HIV wasting syndrome
• *Pneumocystis jirovecii* pneumonia
• Recurrent severe bacterial pneumonia
• Chronic herpes simplex infection (orolabial, genital or anorectal of more than 1 month’s duration or visceral at any site)
• Oesophageal candidiasis (or candidiasis of the trachea, bronchi or lungs)
• Extrapulmonary tuberculosis
• Kaposi’s sarcoma
• Cytomegalovirus infection (retinitis or infection of other organs, excluding liver, spleen or lymph nodes)
• Central nervous system toxoplasmosis
• HIV encephalopathy
• Extrapulmonary cryptococcosis including meningitis
• Disseminated nontuberculous mycobacterial infection

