### Statistics

#### Sample size and power calculations

The study will randomize approximately 467 participants to each of the three study arms during a 36-month enrollment period and will follow participants for 32–66 months. We estimate that loss to follow-up will amount to approximately 15 % of the potential follow-up time, so that the follow-up time available for analysis will average about 41.6 months per study participant, for a total of approximately 1619 person-years of follow-up in each study arm.

For estimating the power of the study, the statistical null hypothesis is that the effect of TS prophylaxis in preventing the first occurrence of a severe event, relative to no prophylaxis, is at least a 35 % reduction in the hazard rate for first occurrences over the study period (i.e., that the hazard ratio, HR, is ≤0.65). Our assumption (alternative hypothesis) for power calculation is that there is no preventive effect of TS, i.e., that HR = 1. The comparison will be based on the upper limit of a two-sided 95 % confidence interval (CI) for the TS effect. An upper limit of less than 35 % – i.e., a reduction significantly less than 35 % at the one-sided 2.5 % significance level – will be considered sufficient evidence for discontinuing TS prophylaxis in this population.

Assuming that the number of severe events follows a Poisson distribution, the mean of the distribution for a participant with average follow-up time (41.6 months) will be approximately 0.236 events, and the probability that the participant will experience at least one severe event will be about 0.210. Assuming that this incidence rate applies to participants taking TS prophylaxis and those without prophylaxis (i.e., no effect of TS prophylaxis), we then expect for the comparison about 196 study participants in both study arms combined to experience at least one severe event, which gives us an expectation of about 85 % power that the upper limit of the 95 % CI for the effect of TS will be less than 35 % [20]. The same consideration applies to the comparison of discontinuation of prophylaxis and CQ prophylaxis.

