### Trial status

The study began recruitment activities at the Ndirande site in November 2012. By mid-February 2015, 900 participants had been recruited. The DSMB evaluated study progress as planned, starting in 2013, and determined that the study was being conducted well and should continue.

During the first year of follow-up in 2013, study investigators noted several pregnancies in study participants who had agreed to practice contraception during the informed consent process. As a result, the study team implemented checks at scheduled follow-up visits to ensure that participants were able to access family planning methods in the community, and to facilitate referral to family planning clinics for contraception. As a result, the incidence of pregnancy in the study population has decreased.

Initially, the trial was designed to recruit 900 participants, with the rationale that the primary endpoint event rate in the entire participant population would be 15 per 100 person-years. As no prospective data were available at the time, this assumption was based on a post-hoc analysis of retrospective data from a similar population. As the study accrued participants, the overall event rate was reviewed regularly due to this uncertainty, and the event rate observed in the study population was 6.8 per 100 person-years as of an interim database lock of July 2014. Sample size determination was revisited at that time, and it was determined that adding approximately 500–600 participants and 2 years of follow-up should provide the expected 350 primary endpoint events needed for primary endpoint analysis. The sponsor agreed to extend and expand the study in early 2015, and a second site, Zomba, was added for recruitment and follow-up in mid-2015. A Standardized Protocol Items: Recommendations for Interventional Trials (SPIRIT) checklist is provided in the supplementary materials as Additional file 1.

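### The power statement for loss of viral suppression (about 75 losses per arm, about 75% power) does not follow from 467 per arm, which gives about 117 losses and about 91% power

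*Protocol article*

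**What the plan says.** Under Analysis of loss of viral suppression, the protocol article applies to this endpoint the same 35% criterion as for severe events, with power calculated under no true effect. It assumes that about 75% of participants on trimethoprim-sulfamethoxazole (TS) remain suppressed, for those "who have the average amount of follow-up (49 months"). It continues: "Then about 75 participants in each of the study arms will be expected to lose their viral suppression during the study". It then puts the power of each pairwise comparison at about 75%.

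Under Sample size and power calculations the arm size is different from what that count implies: "The study will randomize approximately 467 participants to each of the three study arms". That section also states that "the follow-up time available for analysis will average about 41.6 months per study participant", after a deduction of about 15% for loss to follow-up.

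Under Trial status the article records the superseded size: "Initially, the trial was designed to recruit 900 participants". At that point the expected severe-event rate was higher, and about 500–600 participants were added later.

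**The concern.** If 75% keep suppression, 25% lose it, and a quarter of 467 is well above 75. The paragraph prints both its inputs and its result, and they disagree with the arm size stated in the preceding section.

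What is at stake is how informative the virologic comparison is expected to be. The paragraph mentions 80% power and then reports 75%, so the endpoint appears to fall short of a conventional target. On the paragraph's own loss probability and the current arm size, it clears that target comfortably. Loss of suppression has its own 35% criterion and is compared in all three pairs of arms, so a reader will use this figure when judging a result on it.

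**Working it through.** **Inputs**
- 467 per arm (Sample size and power calculations)
- 1:1:1 allocation, so 1:1 within each pair (Overview of the trial)
- probability of losing suppression 1 − 0.75 = 0.25 over 49 months (Analysis of loss of viral suppression)
- margin HR 0.65, true HR 1 (both sections)
- two-sided 95% confidence interval, z = 1.96
- 41.6 months of follow-up after 15% loss (Sample size and power calculations)

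**Formula.** With E events in the two arms together, power = Φ(|ln 0.65| × √E / 2 − 1.96), where |ln 0.65| = 0.4308 (Schoenfeld). As a variant, Freedman's form is Φ(√E × 0.35/1.65 − 1.96).

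**Step 1: check the formula on the primary endpoint.** 2 × 467 × 0.210 = 196 events. Power = Φ(0.4308 × 14.00 / 2 − 1.96) = Φ(1.056) = 85.4%. The article states about 85%, so the method matches.

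**Step 2: reproduce the printed virologic power.** 2 × 75 = 150 losses. Power = Φ(0.4308 × 12.25 / 2 − 1.96) = Φ(0.678) = 75.1% (Freedman 73.8%). The step from 75 losses to 75% power is therefore correct. The fault lies in the count of losses.

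**Step 3: find the arm size behind the count.** 75 / 0.25 = 300 per arm. The superseded design had 900 / 3 = 300 per arm.

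**Step 4: use the current arm size.** 467 × 0.25 = 116.8 losses per arm, or 233.5 per comparison. Power = Φ(0.4308 × 15.28 / 2 − 1.96) = Φ(1.331) = 90.9% (Freedman 90.0%).

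**Step 5: see whether loss to follow-up could explain 75.** This needs an assumption that the article does not state. Under a constant hazard, the probability of loss by 41.6 months is 1 − 0.75^(41.6/49) = 0.2167.

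| Case, 467 per arm unless stated | Losses per arm | Per comparison | Power (Schoenfeld) | Power (Freedman) |
|---|---|---|---|---|
| Printed | 75 | 150 | 75.1% | 73.8% |
| 49 months | 116.8 | 233.5 | 90.9% | 90.0% |
| Follow-up cut by 10% | 106.5 | 213.1 | 88.2% | 87.2% |
| 41.6 months | 101.2 | 202.4 | 86.5% | 85.5% |
| Losses at 49 months × 0.85 | 99.2 | 198.5 | 85.9% | – |
| 500 per arm, 49 months | 125.0 | 250.0 | 92.6% | 91.8% |

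None of these cases comes near 75. To reach 75 from 467, the loss probability would have to be 75/467 = 16%, or the average follow-up about 30 months at the same hazard. The article states neither.

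**Step 6: compare with 80% power.** This needs about 170 losses per comparison (Schoenfeld; Freedman 175). The printed 150 falls short, while every row at the current arm size exceeds it.

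**The case against.** Several things can be said for the paragraph, and some of them stand.

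- **The two follow-up figures may be compatible.** 49 months is the midpoint of 32–66 months, and 0.85 × 49 is about 41.6. One can be potential follow-up and the other follow-up after losses. This stands: the article does not label them, but the difference alone is no contradiction. It also shows that the paragraph matches the current follow-up window, so it is not wholly left over from the old design.
- **The 41.6-month result is not the article's own.** It needs a constant hazard, and the 75% rests on a cited source that is not available here. This stands. Only the 49-month result follows without an added assumption.
- **The origin of 300 per arm is inferred.** The article never gives that number for this calculation. This also stands, but the mismatch with 467 does not depend on where 300 came from.
- **The 80% reference may look like a second error.** A reader might infer that it conflicts with the 85% given for the primary endpoint. It does not. The sentence beginning "Then the same numbers of losses of viral suppression are needed for 80" says only that both endpoints need equal event numbers for that power. With the same margin, confidence level and true HR of 1, that is correct. It never ties 80% to the 196 expected severe events.
- **The error is on the safe side.** It understates the power of a secondary endpoint. This stands and limits how serious the point is, but the printed count and power are still wrong for the current design.

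**Conclusion.** The point holds for the count and the power. With about 467 per arm and a 25% probability of loss, about 117 losses per arm and 233 per comparison are expected, with about 91% power (about 90% by Freedman). The printed 75 losses and 75% power fit only 300 per arm. Carry-over from the 900-participant design is the likely explanation, but not a stated one.

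This result takes the article's 75% suppression probability at face value and, because no effect is assumed, applies it to every arm. If 41.6 months is the relevant follow-up, a constant hazard gives about 101 losses per arm, 202 per comparison and about 86–87% power (85.5% by Freedman).

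A reader might infer that the monitoring board would be misled into treating the endpoint as underpowered. The article does not support that: it lists what the board reviews, including rates of loss of virologic control, and the planned power is not on that list. The primary calculation reproduces at 467 per arm and is unaffected. This is a minor-to-moderate correction of a secondary-endpoint figure that errs low.

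**What to change.** In Analysis of loss of viral suppression, replace the expected losses and power with about 117 per arm (about 233 per pairwise comparison) and about 90–91% at 49 months, based on 467 per arm.

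State whether the suppression probability and the expected losses refer to 49 months of potential follow-up or to the 41.6 months available after loss. If 41.6 months is meant, give about 101 per arm, 202 per comparison and about 86–87% power, and state the constant-hazard assumption. The sentence on 80% power needs no numerical correction.

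The cost is a text edit. The margin, sample size, analysis method and primary power statement do not change, and the corrected power is more favourable than the printed one.

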## Methods/design

This randomized, controlled, open-label, phase III trial will compare standard of care TS prophylaxis and CQ prophylaxis to no prophylaxis. Adults who have been receiving ART for at least 6 months with good clinical response, and who fulfill the eligibility criteria, will be randomized in a 1:1:1 ratio to one of three arms: (1) to continue standard of care TS prophylaxis, (2) to discontinue standard of care TS prophylaxis and begin weekly CQ prophylaxis, or (3) to discontinue standard of care TS prophylaxis. Participants will be asked to return to the research clinic every 4 weeks for the first 24 weeks then every 12 weeks thereafter, and any time they are ill. Participation will last for 32–66 months. Participants who develop a WHO clinical stage 3 or 4 illness, experience a sustained decline in their CD4 count below 200 cells/mm^3^, or who experience ART failure will be placed on standard of care TS prophylaxis (Fig. 1)

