### Study procedures (Table 2)

#### Recruitment

Individuals enrolled in ART clinics at Ndirande and Zomba are eligible after 6 months of taking ART. The ART clinic staff will inform patients in the ART program about the possibility of enrolling in this study. No study-related evaluations are undertaken before obtaining informed consent. The study staff then ask the participant about their plans to remain in the area and their willingness to attend the research clinic for all scheduled and unscheduled follow-up. Potentially eligible participants are then requested to read the informed consent in either English or Chichewa. The informed consent is read and explained verbally in Chichewa to those who are unable to read. This verbal explanation is attended by a witness who will also sign the consent form. After reading or listening, the potential participant is asked to sign the informed consent form. For those who cannot write, a thumbprint is placed on the form, with the signature and date of a witness. The document also allows the participant to indicate how to handle specimens that remain after the study procedures have been completed. Any use of study samples that is outside the scope of the objectives of this protocol will be submitted for prior review and approval by the appropriate Institutional Review Board (IRB). After informed consent is obtained, participants are given a signed copy of the informed consent document and assigned a screening identification number.

**Table 2 Tab2:** Trial flow chart

	Screening	Enrollment	Every 4 weeks for 1st 24 weeks, then every 12 weeks	Additional evaluations every 24 weeks	Final study visit, time of termination	Premature discontinuation of study treatment	Unscheduled Visits
Informed consent	√						
Review of past medical history	√						
Review of current complaints		√	√		√	√	√
Medication history	√		√		√	√	
Bednet use		√	√		√	√	
WHO performance scale		√		√	√	√	
Complete blood count, alanine aminotransferase, creatinine	√			√	√	√	
Urine pregnancy test	√	√^a^	√^a^				
CD4 count	√			√	√	√	
HIV viral load	√			√	√	√	
Filter paper sample		√	√		√	√	
Physical examination	√	√ (limited)	√ (limited)	√	√	√	√
Visual acuity assessment		√		√	√	√	
Provision of medication		√	√				
Pill count and adherence interview			√		√	√	

^a^Urine pregnancy testing will be performed at all study visits only where pregnancy is suspected

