#### Follow-up

Follow-up visits may be one of three types: routine visit, unscheduled visit, or antimalarial efficacy follow-up.

Routine visits occur every 4–12 weeks (every 4 weeks for the first 24 weeks, then every 12 weeks thereafter). Initially, to ensure participant compliance with the study schedule and study drug regimen (if assigned to TS or CQ), participants will be followed every 4 weeks for the first 24 weeks. Thereafter, participants will be followed every 12 weeks, as is the standard of care for ART clinics in Malawi. The encounter will include an interval history, regimen adherence questionnaire (Table 5) and pill counts, questions about off-study drug use and bednet use (Table 4) and a physical examination. In addition, study clinicians will record and/or update any AEs. Dried blood spot samples are obtained, and women of reproductive potential whose last menstrual period was more than 4 weeks prior to this, or whose clinical evaluation suggests pregnancy, will undergo urine pregnancy testing. At routine visits every 24 weeks and the final study visit, approximately 10–12 mL of blood are drawn for determination of CD4 count, HIV viral load, CBC, and ALT and creatinine concentrations; visual acuity is assessed and the WHO performance score (Table 3) is recorded. When participants are followed every 12 weeks, the study team contacts them via cell phone (if number is provided) every 4–6 weeks to ask about their health and to request that they come to the clinic for any current health problems.

**Table 5 Tab5:** Regimen adherence questionnaire

1. How often do you feel that you have difficulty taking your HIV medications on time? By “on time” we mean no more than 2 hours before or 2 hours after the time your doctor told you to take it. ☐ All of the time ☐ Most of the time ☐ Rarely ☐ Never
2. On average, how many days *per week* would you say that you missed at least one dose of your HIV medications? ☐ Every day ☐ 4 to 6 days/week ☐ 2 or 3 days/week ☐ Once a week ☐ Less than once a week ☐ Never
3. When was the last time you missed at least one dose of your HIV medications? ☐ Within the past week ☐ 1 to 2 weeks ago ☐ 3 to 4 weeks ago ☐ Between 1 and 3 months ago ☐ More than 3 months ago ☐ Never

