### Analysis

#### Analysis of the primary endpoint

The primary analysis will compare continuation of TS and discontinuation of TS. It will consist of a 95 % CI for the effect of TS, relative to no prophylaxis, in preventing the occurrence of a severe event, based on proportional hazards (Cox) regression modeling. The TS effect is defined as 1 − HR, where HR is the hazard ratio from the Cox regression model. The analysis will be done according to the intention-to-treat principle; that is, each individual’s data will be analyzed according to the study arm to which the individual was randomized, regardless of the treatment and amount of treatment actually received. Study participants who develop a WHO clinical stage 3 or 4 illness, experience a sustained decline in their CD4 count below 200 cells/mm^3^, or who experience ART failure will be given TS prophylaxis and will continue to be followed in the study. The analytical method for comparing CQ prophylaxis and no prophylaxis (i.e., discontinuation of TS) will be the same as for comparing continuation and discontinuation of TS.

In addition, one or more protocol analyses may be done if there is substantial lack of adherence or administration of a treatment other than the one to which an individual was randomized. This consideration is particularly important since we will be performing noninferiority analysis of discontinuation of TS prophylaxis.

Secondary analyses will compare TS prophylaxis to no prophylaxis, and CQ prophylaxis to no prophylaxis, with respect to the total number of severe events experienced (i.e., including multiple events in individual study participants), using Poisson regression modeling. TS and CQ prophylaxis will also be compared to each other with respect to the first occurrence and all occurrences of severe events. We do not plan to adjust *p* values or CIs for multiple comparisons.

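### The per-protocol rule asks for visits at least every 8 weeks, but the protocol schedules them every 12 weeks after week 24, so perfect attendance fails the rule

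*Protocol article*

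**What the plan says.** The membership rule is in the last paragraph of the section Analysis of loss of viral suppression: "Per-protocol analysis will be performed as a secondary analysis for those who complied with follow-up visits at least every 8 weeks". The same sentence adds adherence to study drug and ART. The article gives no other per-protocol membership rule.

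The visit schedule appears in three places, and they agree:
- Methods/design asks participants to "return to the research clinic every 4 weeks for the first 24 weeks then every 12 weeks thereafter, and any time they are ill".
- The Follow-up section says that after week 24 "participants will be followed every 12 weeks, as is the standard of care for ART clinics in Malawi".
- Table 2 heads its routine-visit column "Every 4 weeks for 1st 24 weeks, then every 12 weeks".

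The Follow-up section lists three kinds of visit: routine, unscheduled and antimalarial efficacy. During the 12-weekly phase "the study team contacts them via cell phone (if number is provided) every 4–6 weeks to ask about their health". That is a call, made only where a number is available, and it is not one of the listed visit types.

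Analysis of the primary endpoint separately allows protocol analyses if adherence is poor or treatments are switched. It adds: "This consideration is particularly important since we will be performing noninferiority analysis of discontinuation of TS prophylaxis". No visit rule is given there.

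**The concern.** A per-protocol set should keep the people who did what the protocol asked. Here the attendance limit is shorter than the interval the protocol itself prescribes, so doing exactly what was asked leads to exclusion.

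Those who remain are not a neutral subset. Some come to clinic often because they are ill or in the 28-day malaria follow-up. Others leave follow-up before an 8-week gap can occur, and these include early deaths, which are primary-endpoint events. The article expects both prophylaxis regimens to prevent malaria, and participants and clinical staff are unmasked, so membership could differ between arms. A comparison within such a set would not show the effect of adhering to the assigned regimen. If the rule were instead changed informally once open-label data had accrued, that would be the discretion that a stated rule is meant to remove.

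**Working it through.** **1. The plan's own power figure.** Inputs from Sample size and power calculations and the Abstract: 467 per arm, 41.6 months average follow-up, 6.8 events per 100 person-years, margin HR 0.65, one-sided 2.5%.
- Person-years per arm: 467 × 41.6/12 = 1,619.
- Mean events per participant: 0.068 × 41.6/12 = 0.236. Probability of at least one: 1 − exp(−0.236) = 0.210.
- First events in two arms: 2 × 467 × 0.210 = 196.
- Power (Schoenfeld): Φ(√196/2 × |ln 0.65| − 1.96) = Φ(7 × 0.431 − 1.96) = 0.854.

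The stated 85% is reproduced, and the per-protocol visit rule plays no part in it.

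**2. Rule against schedule.** Weeks = months × 365.25/(12 × 7). Every scheduled interval after week 24 is 12 weeks, 4 weeks over the limit of 8.

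| Follow-up | Weeks | Weeks after week 24 | Share | Full 12-week intervals |
|---|---|---|---|---|
| 32 months (minimum) | 139.1 | 115.1 | 83% | 9 |
| 41.6 months (average) | 180.9 | 156.9 | 87% | 13 |
| 66 months (maximum) | 287.0 | 263.0 | 92% | 21 |

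A participant with routine visits only fails between weeks 24 and 36. Only someone whose follow-up ends by about week 32 (24 + 8) avoids this without extra visits.

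**3. How many could qualify through extra visits.** The article gives no unscheduled-visit rate, so a range is assumed. Extra visits are simulated as a Poisson process with the same rate for everyone. An interval passes if no gap within it exceeds 8 weeks. With pass probability q per interval, the expected number qualifying per arm is 467 × q^13 at average follow-up and 467 × q^9 at the minimum.

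| Assumed extra visits per year | q | 467 × q^13 | 467 × q^9 |
|---|---|---|---|
| 1 | 0.08 | <0.01 | <0.01 |
| 2 | 0.15 | <0.01 | <0.01 |
| 4 | 0.29 | <0.01 | <0.01 |
| 6 | 0.42 | <0.01 | 0.2 |
| 8 | 0.53 | 0.1 | 1.5 |
| 12 | 0.70 | 4 | 18 |

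Two limits apply. Uneven visit rates would let in a few more people, namely those most often ill. Malaria-efficacy visits are clustered: an episode starting in the first 8 weeks of an interval and followed for 28 days bridges that interval, because the remaining gap is at most 8 weeks. Each of the 13 intervals would still need its own bridge.

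**4. A gentler reading.** Suppose each participant's time counted until the 12-weekly phase starts at week 24. First events in two arms would be 2 × 467 × (1 − exp(−0.068 × 24/52.18)) = 28.8. Power would be Φ(√28.8/2 × 0.431 − 1.96) = 0.21. This reading does not give a useful analysis either.

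**The case against.** The strongest reply is that little depends on this rule. It stands under the viral-suppression heading and is labelled secondary. The sentence that stresses noninferiority concerns optional protocol analyses, triggered by poor adherence or treatment switching, and states no visit rule. A reader might infer that the 8-week set is the trial's key noninferiority check. The document does not say so. The paragraph containing the rule does speak of all primary comparisons, and the rule is the only one stated, so it probably serves those analyses too. That remains an inference.

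A reader might also infer that the trial has no usable analysis beyond intention-to-treat. That is not so. The sentence after the rule plans analyses that censor participants who switch intervention when they develop an indication for TS. Those need no visit rule and stand as written. They deal with switching, though, and not with missed doses or visits.

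It is also fair to say that an empty set is exact only for participants with full follow-up and no extra visits. Beyond that, the size rests on an assumed visit rate, and the possible imbalance between arms has not been quantified.

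Counting telephone calls as visits would not rescue the rule. The article does not class them as visits, and membership would then depend on whether a participant gave a phone number.

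None of this reconciles 8 weeks with 12. If the rule applies to viral suppression alone, it fails there for the same reason.

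**Conclusion.** The contradiction is real and nothing in the article resolves it. As written, the rule excludes participants with full attendance and no extra visits. It leaves a near-empty set, selected on illness visits, malaria-efficacy visits or early end of follow-up. At average follow-up, the expected number qualifying per arm of 467 is below 0.01 at up to 6 extra visits a year and about 4 at 12. These counts rest on the assumed rates and on a constant-rate model. The conflict between rule and schedule rests on neither.

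The consequence is confined to this secondary per-protocol analysis and, probably, to any protocol analysis of the primary endpoint that borrows its definition. The decision on discontinuing TS rests on the intention-to-treat Cox interval. Its margin, its significance level and its 85% power do not change.

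**What to change.** Replace the 8-week criterion with one matched to the protocol's own schedule: attendance at the 4-weekly visits to week 24 and the 12-weekly visits thereafter, each within a stated window. State which endpoints the per-protocol analysis covers, and in particular whether the same definition serves the protocol analyses mentioned under Analysis of the primary endpoint. Whether a deviation leads to exclusion of the participant or to censoring from that time can be left to the SAP.

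The cost is a sentence or two in the protocol or SAP, settled before the analysis. No new data, extra visits or change in sample size are needed.
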